### Participants and Procedure

The study population consists of patients aged 18 years or older with a primary alcohol problem, who are currently following TAU at Tactus Addiction Treatment Institute in the Netherlands. One general inclusion criterion is accessibility and ability to use the Internet, since patients will need to access CBM-training online. Two exclusion criteria apply for the TAU: (1) serious psychiatric illness with a risk to decompensate while decreasing alcohol consumption; and (2) the possibility of severe physical illness as a consequence of decreased alcohol consumption. There are no additional criteria for participation in this study.

Patients for the training are recruited by therapists at Tactus Addiction Treatment Institute. After the regular intake procedure, including baseline questionnaires, the TAU starts. Before the patient reaches the goal-setting assignment, the therapist will inform the patient about the CBM training and provide the patient with further information about the study. If the patient wants to participate, an informed consent form will be provided to patients by the therapist. After signing the form, the patient receives login credentials for the CBM training from the researcher.

After finishing registration, the patient is randomly assigned to the Alcohol Avoidance Training or to the placebo training, and receives an email with a link to the CBM training website. After logging in, the patient receives instructions about the training. At the start of each session, the patient is asked to complete the additional questionnaires for the purpose of this study, consisting of self-reported weekly alcohol consumption and desire for drinking. Each of the eight training session takes about 10-15 min. The first training session is preceded by an (online) preassessment and the final training session is followed by an (online) postassessment. Three and six months after the postassessment, each patient will receive online follow-up questionnaires. In case of nonresponse, the patient will be reminded by email or phone to complete the questionnaire.

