**Figure 2 figure2:**
[figure not shown]
An example of Approach-Avoidance Training.

**Table 2 table2:** Measurement instruments: purpose, measures and time points.

Purpose and measure^a^		Baseline TAU^b^	Preassessment		Training		Postasssessment		Posttest TAU		Follow-up	

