### Sample Size Calculation

An a priori statistical power analysis (G-power) was conducted to determine the necessary number of participants. The primary outcome measure is a reduction in alcohol consumption. To obtain an estimate of the effect size to be expected, studies describing previous Alcohol Avoidance Training interventions were inspected [21,23]. In both these studies, a relative increase of 20% was observed in effectiveness of TAU + CBM as compared to TAU. The proportion of patients reaching long-term abstinence increased by 13% from 41%-54% [23]. Although in these studies a different dependent measure was used (prolonged abstinence from alcohol), we assume a similar increase in success rate of +13 percentage points as effect size. It has been shown that the Web-based treatment resulted in a 68% success rate (ie, reaching the low-risk drinking criterion) [52]. When extrapolating that to this study, a +13 percentage points additional effect of the Alcohol Avoidance Training is predicted to result in 81% achieving the safe drinking criterion (beta>.80; alpha (one-tailed) <.05). Based on these parameters, 152 patients are needed within a condition to show the hypothesized effects using a Fisher’s exact test for proportions in two independent samples.

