### Statistical Analyses

Analyses will be conducted in agreement with intention-to-treat principle. Missing data points will be handled using multiple imputation [53]. One-way ANOVAs and χ²-tests will be performed to see if there are any significant differences at baseline between the two CBM training conditions (Avoid Alcohol vs placebo) for any of the demographic variables or outcome measures. Nonsignificant differences will indicate successful randomization. To determine the primary outcome, a logistic regression analysis will be used to test the differences in the proportion of patients reaching the low-risk drinking criterion between the CBM Alcohol Avoidance Training and CBM placebo condition, both at posttest and at follow-up. If necessary, baseline confounders will be controlled for, and significant interaction effects will be further investigated using post hoc *t*-tests (independent samples *t*-test and paired samples *t*-test). Effect sizes on clinically relevant outcomes at postintervention and follow-up will be calculated by Cohen’s d using the means and pooled standard deviations of the measurements of the conditions. Effect sizes of .56-1.2 are considered large, .33-.55 are considered moderate, and less than .33 are considered small [54]. Repeated measures ANOVAs will be conducted to test for differences between the CBM Alcohol Avoidance Training and the CBM placebo condition on the secondary outcomes general health condition, depression, anxiety and stress. Mediation analyses will be conducted by applying the analytic procedure according to Preacher and Hayes [55] and Hayes [56] to examine whether a change in approach bias is mediating the Alcohol Avoidance Training effects on our primary outcome measure. Logistic regression analyses will be used to assess whether patient characteristics moderate the effect of the Alcohol Avoidance Training on our primary outcome measure. The procedure proposed by Baron and Kenny [57] will be adopted. Descriptive statistics will be used to investigate to what extent patients adhered to the Alcohol Avoidance Training (in terms of timing, frequency, and duration of sessions) and to what extent patients found the Alcohol Avoidance Training both acceptable and credible (testing adherence, acceptability, credibility).

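### The repeated measures ANOVA for health status, depression, anxiety and stress leaves the treatment test open and pre-sets no adjustment for the baseline value, which costs power

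*Protocol article*

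**What the plan says.** The Statistical Analyses section states: "Repeated measures ANOVAs will be conducted to test for differences" between the two training conditions on four secondary outcomes, namely general health condition, depression, anxiety and stress. It names neither the levels of the time factor nor the effect that carries the treatment comparison.

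Baseline adjustment is conditional: "If necessary, baseline confounders will be controlled for". The same sentence adds that "significant interaction effects will be further investigated using post hoc" t-tests, and names both the independent-samples and the paired form. It comes directly after the primary logistic regression and before the ANOVA is introduced.

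Table 2 ("Measurement instruments: purpose, measures and time points") ticks the health symptom scale and the depression, anxiety and stress scale at TAU baseline, TAU post-test and follow-up. The Participants and Procedure section gives two follow-ups: "Three and six months after the postassessment, each patient will receive online follow-up questionnaires". That makes one baseline and up to three post-baseline measurements. The baseline questionnaires belong to the regular intake, before consent and randomisation.

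**The concern.** The hypothesis in the Aims section compares the training with placebo, so it concerns a difference between arms after randomisation. A repeated measures ANOVA with baseline as a time level offers two tests, and neither targets that difference well.

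- The condition main effect averages in the baseline value, where no training effect can exist.
- The condition-by-time interaction compares changes from baseline. At any correlation below 1 this is less precise than adjusting for baseline. With several visits it also spreads the question over several degrees of freedom.

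Because the text does not choose between the two, the treatment test could be settled after the data are seen. The sample size covers only the binary primary outcome, so the secondary outcomes have no planned power to spare. Paired t-tests compare times within an arm. Both arms receive TAU, so improvement within an arm is expected without any effect of the training.

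**Working it through.** **The plan's own figure.** The documents give no power for the secondary outcomes. The only stated figure is 152 per arm for the primary outcome (68% against 81%, one-tailed 0.05, power 0.80, Fisher's exact test). It is reproduced: exact one-sided power is 0.803 at 152 per arm and 0.7999 at 151.

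**Inputs.** From the protocol: n = 152 per arm; one baseline and up to k = 3 post-baseline visits. Assumed, because the documents do not give them: unit variance, the same correlation ρ between any two visits, an effect δ that is constant after baseline, two-sided 0.05, no dropout.

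**Per-arm variances.**
- Mean of the post-baseline visits: Vp = (1 + (k−1)ρ)/k
- The same, adjusted for baseline: Va = Vp − ρ²
- Mean post-baseline minus baseline (change score): Vc = Vp + 1 − 2ρ
- Mean of all k+1 levels: Vm = (1 + kρ)/(k+1), with the effect shrunk to δ·k/(k+1)
- One visit adjusted for baseline: 1 − ρ²

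Let R be the non-centrality of a 1-df test divided by that of the adjusted averaged contrast. With the latter set at 80%, power = Φ(2.802·√R − 1.960).

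**At ρ = 0.5, k = 3.** Vp = 0.667, Va = 0.667 − 0.25 = 0.4167, Vc = 0.667, Vm = 0.625.
- Adjusted contrast: 1/0.4167 = 2.4, set at 80%.
- Change-score contrast: 1/0.667 = 1.5; R = 0.625; Φ(2.215 − 1.960) = 0.60.
- Condition main effect: 0.75²/0.625 = 0.90; R = 0.375; Φ(1.716 − 1.960) = 0.40.
- Omnibus 3-df interaction: non-centrality 2.802² × 0.625 = 4.91 on 3 and 906 df, power 0.43. The non-centrality equals that of the change-score contrast, so the drop from 0.60 to 0.43 is purely the cost of the extra degrees of freedom.
- Post-baseline visits only, unadjusted: 1/0.667 = 1.5; power 0.60.
- One visit, adjusted: 1/0.75 = 1.33; R = 0.556; power 0.55.

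**Range, k = 3, adjusted averaged contrast at 0.80:**

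| Test | ρ = 0.4 | 0.5 | 0.6 | 0.7 |
|---|---|---|---|---|
| Change-score contrast | 0.547 | 0.601 | 0.650 | 0.694 |
| Condition main effect, baseline included | 0.468 | 0.404 | 0.335 | 0.265 |
| Omnibus 3-df interaction | 0.383 | 0.431 | 0.478 | 0.522 |
| Post-baseline only, unadjusted | 0.670 | 0.601 | 0.516 | 0.415 |
| Single visit, adjusted | 0.527 | 0.551 | 0.571 | 0.589 |

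**One post-baseline visit (k = 1).** R = (1 − ρ²)/(2(1 − ρ)) = (1 + ρ)/2, which is 0.75 at ρ = 0.5. Change-score power is 0.68 (0.62 to 0.76 for ρ from 0.3 to 0.8).

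**Effect at the last visit only.** Against a baseline-adjusted test of that visit at 80%, the omnibus interaction has 0.63 to 0.79 for ρ from 0.3 to 0.8, over three or four levels.

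**The case against.** A condition-by-time test in a randomised trial is a valid comparison between arms, so the issue is efficiency, not bias. The article never writes that baseline is a time level, and an article may leave model details to a fuller plan. Both statements are fair. The second does not rescue the method: if baseline is left out of the time factor, the unadjusted comparison of the post-baseline visits still loses power (41% to 67% in the table).

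A reader might infer three stronger things that the documents do not support.

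- *The plan roughly halves the power.* The 40% and 43% figures arise with four levels, an assumed correlation of 0.5, a constant effect, and either the main effect or the 3-df omnibus test as the treatment test. The 43% also sets a 3-df test against a 1-df test; a baseline-adjusted 3-df test would itself have only about 64%. The protocol states no correlation, effect pattern or choice of test.
- *Gains within an arm will be read as training effects.* Independent-samples t-tests are named beside the paired ones, both depend on a significant interaction, and their sentence is attached to the primary analysis. The ANOVA's declared purpose is to compare the conditions. A paired t-test does suit a repeated continuous score better than a binary criterion, so a link to the secondary outcomes is plausible, but it is not written.
- *The ANOVA forces a complete-case analysis.* Multiple imputation is planned, and tests can be pooled over imputations.

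**Conclusion.** The point holds as a matter of efficiency and of an unspecified treatment test. Under every reading of the planned ANOVA, a contrast adjusted for the outcome's own baseline value would be more precise. Like for like, 80% power becomes about 60% at a correlation of 0.5 with three post-baseline visits (55% to 69% for 0.4 to 0.7), or 68% with a single post-baseline visit. A fall to about 40% to 43% is possible at that correlation but conditional on the extra assumptions above. The sizes rest on equal variances, equal correlations, two-sided 0.05 and no dropout. That baseline is a time level is inferred from Table 2. No stated figure in the protocol is wrong, and the primary analysis and its sample size are untouched. The change is worth making but is not critical.

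**What to change.** Replace the repeated measures ANOVAs with a linear mixed model on the post-baseline visits (TAU post-test, 3 and 6 months), with condition, visit, condition-by-visit, the baseline value of the outcome, and type of TAU, which is already the minimisation factor.

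Name one treatment contrast per outcome as the test, for example the between-arm difference averaged over the post-baseline visits. This naming matters: under the assumptions above, a single-visit contrast has only about 55% power at a correlation of 0.5 where the averaged contrast has 80%. Report the between-arm difference at each visit with its 95% interval as supportive.

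State that conclusions about the training rest on between-arm contrasts, not on paired t-tests within an arm.

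The cost is a few sentences in the analysis plan. Standard software fits the model, and no new data or patients are needed.

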### Aims and Hypotheses

The aim of the current study is to investigate the effectiveness of online CBM Alcohol Avoidance Training as an adjunct to TAU in an outpatient treatment setting. Patients receive eight sessions of either the active or placebo version of the CBM Alcohol Avoidance Training during their TAU. The primary goal is to test the effects of this adjunct CBM on alcohol use immediately after finishing the intervention and three and six months later, by looking at the changes in the level of alcohol consumption over a week. The primary outcome measure is the percentage of the patients reaching the low-risk drinking level, defined as <22 standard units/week for men and <15 for women [29]. It is expected that more patients in the experimental condition will reach low-risk drinking level. Furthermore, it is hypothesized that the CBM intervention decreases or reverses the approach bias, and these changes are expected to mediate the effects on alcohol use [23]. An improvement in health status and a decrease in depression, anxiety and stress for patients in the training condition, compared to the placebo condition, are expected as secondary outcomes. To investigate who benefits most from the training, possible moderators will be examined. Automatic impulses may be controlled by cognitive capacity available to inhibit these impulses. Refusal self-efficacy is considered such a cognitive resource. Following this assumption, CBM interventions can yield benefits, especially for those with a relatively weak cognitive control over their impulses to drink [12,30-32]. In line with the predictions from dual process models and prior CBM trials [12], it is expected that for patients with a low baseline self-efficacy, the additional effect of the Alcohol Avoidance Training will be stronger. Similarly, time-varying self-efficacy is expected to partially mediate the CBM effect as repeated experiences of successful coping due to stronger avoidance responses will enhance refusal self-efficacy. Patients’ adherence and perceptions of treatment acceptability, and credibility will also be examined.

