#### Approach-Avoidance Tendencies

Approach-avoidance tendencies are assessed with the AAT pre- and posttraining [23]. The tests consist of 172 trials; 12 practice trials (gray squared pictures) and 160 assessment trials, the latter subdivided into four blocks of trials. Participants randomly receive either set A or set B during assessment. Each set consists of 40 pictures (20 depicting alcoholic beverages and 20 soft drinks) and those are presented 4 times: 2 formats (tilted to the left or right) x 2 repetitions. Alcoholic beverages and soft drink pictures are presented equally often in both formats.

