### Primary and Secondary Outcome Measures

The primary outcome measure for this study will be *the proportion of patients reporting alcohol consumption below low-risk drinking limits* (<22 standard units/week for men and <15 for women) [29], since achieving safe drinking is the primary aim of alcohol addiction care. This will be assessed using the TLFB method [40]. As it was not feasible to verify whether all participants met this threshold at the start of treatment and with the knowledge that a previous trial with a similar target group showed that enrolled participants only very rarely report below-threshold consumption levels at baseline [35]-, we allowed all patients to enroll in the study. If necessary, corrections will be made in the analyses.

Secondary outcome measures include changes in approach bias measured by an AAT in the preassessment and postassessment. An AAT bias index is calculated as the difference between the median reaction time scores for pushing pictures of one category (alcoholic beverages or soft drinks) and the median reaction time score for pulling pictures of that category. Median scores are used to minimize the influence of outliers. Positive scores indicate approach tendencies whereas negative scores indicate avoidance tendencies. Furthermore, it is investigated whether the added effect on treatment outcome is mediated by the amount of change in approach bias and who benefits most from training by identifying patient characteristics that moderate the outcome of the training. Other secondary outcome measures are general health condition, depression, anxiety and stress, intervention credibility and patient satisfaction.

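### The mediation analysis uses change in approach bias as the mediator and states no adjustment for the preassessment bias, so the mediated effect can be shrunk or take the wrong sign unless drinking depends only on the difference

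*Protocol article*

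**What the plan says.** All references are to the protocol article.

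- **Hypothesis.** Aims and Hypotheses expects that "the CBM intervention decreases or reverses the approach bias, and these changes are expected to mediate the effects on alcohol use".
- **Measurement.** Under Approach-Avoidance Tendencies, "Approach-avoidance tendencies are assessed with the AAT pre- and posttraining". The index is defined under Primary and Secondary Outcome Measures: "An AAT bias index is calculated as the difference between the median reaction time scores for pushing pictures of one category" and the median for pulling pictures of that category. A preassessment value is therefore planned for each patient.
- **Mediator and bias outcome.** The same section states "Secondary outcome measures include changes in approach bias measured by an AAT in the preassessment and postassessment", and asks whether the added effect is "mediated by the amount of change in approach bias". Statistical Analyses repeats the change form: "to examine whether a change in approach bias is mediating the Alcohol Avoidance Training effects on our primary outcome measure".
- **Covariates.** The mediation sentence names a cited procedure, a mediator and an outcome, and lists no covariates. The only adjustment wording is "If necessary, baseline confounders will be controlled for". It comes straight after the primary logistic regression. Baseline tests between arms are described before that, and their non-significance is read as showing that randomisation worked.
- **Test of training on bias.** None is named. The repeated measures ANOVAs list health, depression, anxiety and stress only.

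**The concern.** Randomisation protects the comparison of arms on approach bias. It does not protect the path from bias to drinking, which is an observational association within arms. A raw change score is negatively correlated with its own starting value. If the starting value is not in the outcome equation, the coefficient of change therefore carries part of the starting value's effect with its sign reversed.

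Balance between arms does not address this. Two perfectly balanced arms can still have a strong within-arm relation between starting bias and drinking, so an adjustment rule triggered by imbalance would stay silent. At stake is the trial's test of mechanism: a real mediated effect could be missed, or one of the wrong sign reported.

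**Working it through.** **The plan's own figure.** For 68% against 81%, one-tailed alpha 0.05 and Fisher's exact test, exact power is 0.7999 with 151 per arm and 0.8030 with 152. The stated 152 reproduces. It is used below only as the trial size.

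**Inputs not in the article.** The pre-post correlation of the index (ρ) and all path coefficients are assumptions. Both scores are scaled to SD 1.

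**Step 1: what the coefficient of change estimates.** Let the log odds of low-risk drinking depend on β1·pre + β2·post, and let D = post − pre. Within an arm, cov(D, pre) = ρ − 1, cov(D, post) = 1 − ρ and var(D) = 2(1 − ρ). To a linear approximation the coefficient of D alone is

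[β1(ρ − 1) + β2(1 − ρ)] / [2(1 − ρ)] = (β2 − β1)/2, whatever ρ is.

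It equals β2 only if β1 = −β2, that is, if the outcome depends on the difference alone.

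**Step 2: numbers.** Take a training effect on bias of a = −0.5 SD. The formula column is a(β2 − β1)/2. The simulated columns come from a logistic model with 1,000,000 patients and ρ of 0.2, 0.5 and 0.8.

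| What drives outcome | β1 | β2 | True a·β2 | Formula, change alone | Simulated, change alone | Simulated, preassessment bias added |
|---|---|---|---|---|---|---|
| Post-training bias only | 0 | −0.5 | 0.25 | 0.125 | 0.119 to 0.122 | 0.250 to 0.254 |
| Both | −0.25 | −0.5 | 0.25 | 0.0625 | 0.056 to 0.059 | 0.249 to 0.250 |
| Starting bias only | −0.5 | 0 | 0 | −0.125 | −0.118 to −0.123 | −0.002 to 0.001 |
| The difference itself | 0.5 | −0.5 | 0.25 | 0.25 | 0.249 to 0.250 | 0.248 to 0.250 |

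**Step 3: change or post score.** β1·pre + β2·post = (β1 + β2)·pre + β2·D. Once preassessment bias is in the model, change and post score have the same coefficient. The simulations agree.

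**Step 4: at the trial's size.** Settings: 152 per arm; training effect on bias −0.4 SD; effect of bias on outcome −0.4 log odds per SD; baseline drinking −0.6; correlation of starting bias with baseline drinking 0.2. Results are for ρ = 0.3 / 0.5, in repeated runs of several hundred trials per setting.

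| Mediation model | Post bias drives outcome: mean indirect effect | Significant | Only starting bias predicts outcome: significant, wrong sign |
|---|---|---|---|
| Change alone | 0.052 / 0.048 | 18% / 16% | 51% / 42% |
| Change + baseline drinking | 0.083 / 0.080 | 27% to 33% | 34% / 25% |
| Change + preassessment bias | 0.153 / 0.153 | 73% / 68% | about 5% (false positives) |
| Post score + preassessment bias + baseline drinking | 0.165 / 0.165 | 74% / 72% | about 5% (false positives) |

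Against 0.165, change with baseline drinking recovers 0.083/0.165 = 50% and 0.080/0.165 = 48%. Change alone recovers 0.052/0.165 = 32% and 0.048/0.165 = 29%. With 500 trials the standard error of a percentage near 50% is √(0.25/500) = 2.2 points, so these percentages are approximate.

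**Step 5: training effect on bias.** Power = Φ(d/√(2v/152) − 1.96), with v = 2(1 − ρ) for change and v = 1 − ρ² with baseline adjustment. Take d = 0.33, the article's boundary between small and moderate. At ρ = 0.3, change gives Φ(0.33/√(2 × 1.4/152) − 1.96) = Φ(0.47) = 68%, and adjustment gives Φ(0.33/√(2 × 0.91/152) − 1.96) = Φ(1.06) = 85%. The pairs are 82% and 91% at ρ = 0.5, and 96% and 98% at ρ = 0.7.

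**The case against.** The strongest case against has four parts.

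- **Silence is not exclusion.** A reader might infer that the plan leaves preassessment bias out. The article does not say so. It lists no covariates, it is a condensed text, and a fuller plan may add them. That stands. What remains is that the text fixes the mediator as change, states no adjustment for its starting value, and ties its only adjustment wording to a question that does not bear on this path.
- **Change is not itself the error.** A reader might conclude that the change score must be replaced by the post score. Step 3 shows that this gains nothing once preassessment bias is in the model. That stands in full.
- **The distortion is conditional.** Aims and Hypotheses expects the changes in bias to mediate drinking. If outcome depends on the difference alone, omitting preassessment bias causes no bias. In that case, with baseline drinking in the model, change gives 0.163 to 0.164 against 0.161 to 0.166 fully adjusted, and detects it somewhat more often (76% to 83% against about 74%). This stands, but the article does not argue for that restriction, and the adjusted model stays valid under it.
- **The largest contrasts have two causes.** The fall to a third, and the wrong-sign rates of 42% to 51%, come from omitting baseline drinking as well as preassessment bias. This stands. With baseline drinking included, the figures are about half and 25% to 34%.

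A reader might also infer that the training effect on bias is wrongly estimated. It is not: under randomisation a change-score comparison is unbiased. It loses only precision, little at high ρ, and the article names no test for it.

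**Conclusion.** The point holds in a limited form. The mediator is specified as change, with no stated adjustment for a preassessment index that the trial collects, and the existing adjustment rule would not supply it. Unless drinking depends only on the difference, the mediated effect is then distorted. Under the assumed coefficients, with 152 per arm and ρ of 0.3 to 0.5, it shrinks to about half (about a third if baseline drinking is also omitted). If only starting bias predicts outcome, it is significant with the wrong sign in roughly 25% to 50% of trials.

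These sizes rest on correlations and path coefficients that the article does not give. The direction of the distortion, and its absence when β1 = −β2, follow from the algebra for equal SDs. The analysis is secondary and explanatory, and neither the primary comparison nor the sample size is touched. It is still worth correcting, because mediation is a stated hypothesis and the remedy costs almost nothing.

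**What to change.** In Statistical Analyses, state that:

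1. The preassessment AAT index and baseline weekly consumption are fixed covariates in both mediation equations (bias on condition; low-risk drinking on bias and condition), whatever the baseline tests show. Table 2 lists weekly consumption at both the TAU baseline and the preassessment, so name which one is used.
2. The preassessment AAT index is a covariate in any comparison of approach bias between arms.

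Change may stay as the mediator in both sections.

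Cost: wording only, since every variable is already collected. Each model gains one or two parameters, and detection is slightly lower if outcome truly depends on the difference alone.
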